**Background:**

Many randomized clinical trials have established the efficacy of highly effective regimens for the treatment of patients with drug-susceptible tuberculosis; however, they must be administered for a minimum of six months to achieve optimal results. [1]. Non-adherence to treatment remains a major problem even with these six-month regimens. To address this, directly observed therapy (DOT) has been advocated as a standard of care worldwide and is a vital component of the WHO’s global strategy for TB control. [2]. The Revised National Tuberculosis Control Programme (RNTCP) of the Government of India is based on the global strategy of WHO. However, the administrative burden of providing DOT for all patients is considerable and the RNTCP recommends full DOT only for the initial intensive phase of treatment and partial DOT for the continuation phase. Thus, there is a need for new drugs that would permit significant shortening of treatment.

The demonstration of anti-mycobacterial activity of the fluoroquinolone group of drugs has opened a window of opportunity to address this particular need for the shortening of the duration of treatment. [3,4] A randomized clinical trial by the TRC has shown that by using ofloxacin in the intensive phase of a 4-month regimen, it is feasible to achieve a cure rate of 99% at the end of treatment and a relapse rate of less than 5% over 24 months of post-treatment follow-up in patients with drug susceptible bacilli. [5] Since then, data has emerged about newer fluoroquinolones, in particular moxifloxacin, gatifloxacin, levofloxacin, sparfloxacin, clinafloxacin, lomefloxacin, and others, which have more potent anti-mycobacterial activity both in terms of bactericidal activity and sterilizing activity. [6,7,8]

Of the currently available fluoroquinolones, moxifloxacin and gatifloxacin have been shown to have excellent activity *in vitro* and in animal models of tuberculosis, a favorable pharmacokinetic profile (serum half-life of 10-12 hours), and excellent safety profiles. However, these drugs have not been evaluated for tuberculosis treatment and have only been formally evaluated in treatment durations of 2 week or less for acute bacterial respiratory infections such as community acquired pneumonia and acute exacerbations of chronic sinusitis. Therefore, there is a need to evaluate the safety of more prolonged dosing of moxifloxacin and gatifloxacin and to assess their activity against clinical tuberculosis.

Moxifloxacin is a new 8-methoxy fluoroquinolone antibiotic with excellent activity against *Mycobacterium tuberculosis* both *in vitro* and in animal models. The MIC for clinical isolates of *Mycobacterium tuberculosis* ranges from 0.12 to 0.5 ug/ml and it is the most active among the newer set of fluroquinolones. [9,10,11] In an experimental study on female Swiss mice infected with H37Rv and treated with various drug dosages, moxifloxacin was more potent than sparfloxacin and clinafloxacin, at the 100 mg/kg dosage comparable to that of isoniazid.

The recommended dosage of moxifloxacin is 400 mgm.

Gatifloxacin is a new broad-spectrum fluoroquinolone which is active against gram-positive, gram-negative and anaerobic organisms and has been used for the treatment of acute bacterial exacerbation of chronic bronchitis, acute sinusitis, community-acquired pneumonia, uncomplicated and complicated urinary tract infections, pyelonephritis and uncomplicated gonorrheal infections.

Quinolones inhibit DNA gyrase and topoisomerase IV. DNA gyrase is an essential enzyme that is involved in the replication, transcription and repair of bacterial DNA. Topoisomerase IV is an enzyme known to play a key role in the partitioning of the chromosomal DNA during bacterial cell division.

Gatifloxacin is well absorbed from the gastrointestinal tract after oral administration and can be given without regard to food. The absolute bioavailability of gatifloxacin is 96%, and peak plasma concentrations usually occur in one to two hours. Mean steady-state peak and trough plasma concentrations attained following a dosing regimen of 400 mg once daily are approximately 4.2 µg/mL and 0.4 µg/mL, respectively, for oral administration and 4.6 µg/mL and 0.4 µg/mL, respectively, for IV administration.

Gatifloxacin undergoes limited biotransformation in humans. In vitro studies with cytochrome P450 isoenzymes indicate that gatifloxacin neither inhibits CYP3A4, CYP2D6, CYP2C9 or CYP1A2, nor induces hepatic enzymes. Therefore, it is unlikely that gatifloxacin will alter the metabolic elimination of itself or other drugs.

Gatifloxacin undergoes both glomerular filtration and tubular secretion and greater than 70% is excreted as unchanged drug.

The recommended dosage of gatifloxacin is 400 mgm.

Since gatifloxacin and moxifloxacin have anti-mycobacterial activity superior to that of ofloxacin and their safety profile have been shown to be excellent, albeit when used for short duration (up to 14 days), they may prove to be useful drugs to shorten treatment duration for tuberculosis, when used along with other first-line anti-TB drugs. Since an ofloxacin-containing 4-month regimen has been shown to be highly effective, the substitution of either moxifloxacin or gatifloxacin for ofloxacin could be expected to fare even better.

It is therefore proposed to carry out a study to assess the tolerability of moxifloxacin and gatifloxacin containing regimens in patients with smear-positive pulmonary tuberculosis with particular reference to their long term use, and to assess the efficacy of these regimens in terms of culture conversion at 2 months, results at the end of treatment and relapse rates up to 24 months of follow-up.

**Setting:**

The study will be carried out by the Tuberculosis Research Centre in Chennai and Madurai, in collaboration with our partners, the Institute of Thoracic Medicine, RNTCP Clinics of the Corporation of Chennai, Government Thiruvatteeswarar Hospital, the Ramakrishna Mutt Charitable Dispensary, the Chest Clinics of the Government Royapettah Hospital, the Government Dispensary Saidapet, all in Chennai, and the Chest Clinic of the Rajaji Hospital in Madurai.

**Patients:**

Patients aged 18 years and above residing in or around Chennai or Madurai will be eligible for enrollment to the study. They should not have anti-TB treatment in the past or should have had less than one month of treatment (but less than one week in the preceding one month before enrollment in the study).

They should have sputum culture-positive pulmonary tuberculosis (at least two cultures should be positive). Patients will be enrolled to the study when two sputum smears are positive and will be retained for analysis only if two cultures are positive.

They should consent to attend the treatment centre for supervised treatment for 6 months and for home visits by the staff of the center.

They should give written informed consent.

The following patients will not be eligible for the study:

Those with

- body weight less than 30 kg
- hepatic or renal disease as evidenced by clinical or biochemical abnormalities
- diabetes mellitus
- a history of seizures
- psychiatric illness
- an abnormal electrocardiogram or those on anti-arrhythmic medication
- Those in a moribund state
- Those sero-positive for HIV antibodies
- Pregnant or lactating women

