**Outcome measures:**

The following outcome measures will be compared between regimens:

a) Sputum culture conversion at 2 months of treatment,

b) Favourable bacteriological response at end of treatment

c) Unfavourable bacteriological response at end of treatment

d) Doubtful bacteriological response at end of treatment

e) Relapse after successful treatment.

f) Adverse reactions to anti-TB drugs, especially to moxifloxacin and gatifloxacin.

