**Clinical assessments and Investigations:**

*Baseline:*

History of present complaints and past medical history.

Detailed clinical examination including testing for aquity of vision and colour vision.

Detailed history of previous treatment for tuberculosis and history of use of quinolones and anti-arrhythmic medication. All available prescriptions slips will be scrutinized and recorded.

Assessment by a social worker for domestic stability, family history, occupational history and sociological suitability for likely adherence to treatment protocol.

Home visit by a social worker and health visitor.

At least four sputum specimens will be examined by smear (fluorescent microscopy) and culture (with LJ medium) for *Mycobacterium tuberculosis*. Positive cultures will be identified by catalase production at 68°C and PNB test. Drug susceptibility tests for streptomycin, isoniazid, rifampicin, ethambutol, moxifloxacin and gatifloxacin will be done on positive cultures.

X-ray chest PA view

Urinalysis for albumin, sugar, bile pigments, acetyl isoniazid, rifampicin and for cytology.

ECG in 12 leads. The ECGs will be interpreted by a cardiologist.

Total and differential white cell counts, red blood cell count, haemoglobin estimation, platelet count.

Random blood sugar, blood urea, serum creatinine, serum uric acid, serum bilirubin, serum alanine and aspartate transaminase, serum alkaline phosphatase and gamma glutamy transaminase (GGT).

ELISA for HIV antibodies.

*During treatment:*

Every month during the treatment phase the following will be done:

Clinical examination

Weight will be recorded

Monitoring for adverse reactions to drugs, especially moxifloxacin and gatifloxacin.

Three sputum specimens will be examined by smear (fluorescent microscopy) and culture (LJ medium) for *Mycobacterium tuberculosis* and identification and drug susceptibility tests for isoniazid, rifampicin, ethambutol, moxifloxacin and gatifloxacin will be carried out on positive cultures.

ECG in 12 leads

Urinalysis will be done for albumin and cytology

X-ray Chest PA view at the 2nd monthly examination and at the end of treatment

Total and differential white cell counts, red blood cell count, haemoglobin estimation and platelet count at the time of the 2nd and 4th monthly examinations.

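### The two-culture rule is not limited to efficacy, so patients who took study drugs drop out of the adverse-reaction comparison

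*Supplement*

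**What the plan says.** **Who is analysed.** Under Patients, the protocol enrols on two positive sputum smears and adds that patients "will be retained for analysis only if two cultures are positive". It says analysis without qualification. Neither the protocol nor its amendments define a separate population for safety.

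**What safety is for.** The Background closes by stating that the study is to "assess the tolerability of moxifloxacin and gatifloxacin containing regimens in patients with smear-positive pulmonary tuberculosis", with emphasis on long-term use. Outcome measures lists, among the outcomes to be compared between regimens, "Adverse reactions to anti-TB drugs, especially to moxifloxacin and gatifloxacin". Definition of Outcome Measures does not define this item: it gives no denominator, window or counting rule.

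**When reactions are looked for.** In Clinical assessments and Investigations, the treatment-phase list opens with "Every month during the treatment phase the following will be done" and includes "Monitoring for adverse reactions to drugs, especially moxifloxacin and gatifloxacin" and a 12-lead ECG. The follow-up list has a monthly clinical examination but neither of those two items. Treatment Regimens sets 4 months for Regimens 1 and 2 and 6 months for Regimen 3. The October 2005 amendment sets 26 + 26 and 26 + 52 doses respectively.

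**The concern.** Treatment starts on smear, before culture results are known. A smear-positive patient who takes moxifloxacin or gatifloxacin, has a reaction and turns out to lack two positive cultures belongs to the population named in the tolerability aim. The Patients section nevertheless removes that patient. The Background says these drugs had been formally evaluated only for courses of two weeks or less, so information on longer exposure is part of the reason for the trial and should not be discarded.

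The second, lesser concern is the length of observation. If reactions are counted as a simple percentage over each patient's treatment phase, the control arm has half as much time again in which to record one.

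**Working it through.** **1. The enrolment figure.** Sample size gives 2 × 0.95 × 0.05 × (1.64 + 1.28)² / 0.05² = 324.0 per regimen (the plan prints 323). Then 3 × 323 = 969, and 969 / (0.9 × 0.9) = 1196, rounded in the plan to 1200. The figure reproduces. Equal thirds, 400 per arm, are assumed below.

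**2. How many dosed patients the rule removes.** The documents give no rate. Assumed range:

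| Excluded (assumed) | Of 1200 | Per arm of 400 | Interval width × 1/√(1−c) | Chance of at least one event of true risk 0.5% in an arm |
|---|---|---|---|---|
| 0% | 0 | 0 | 1.00 | 1 − 0.995^400 = 86.5% |
| 2% | 24 | 8 | 1.01 | 86.0% |
| 5% | 60 | 20 | 1.03 | 85.1% |
| 10% | 120 | 40 | 1.05 | 83.5% |
| 15% | 180 | 60 | 1.08 | 81.8% |

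**3. Does the exclusion bias the comparison?** The Patients section does not say which cultures count. It states the rule as an entry criterion, and the baseline list calls for at least four specimens for smear and culture, so pre-treatment cultures are the natural reading. Randomised arms should then lose similar shares. Suppose 10% are excluded in each arm, that true risks among those kept are 10% and 20%, and that excluded patients have double the risk:
- Kept patients only: 20% / 10% = 2.0.
- All dosed patients: (0.9 × 20% + 0.1 × 40%) / (0.9 × 10% + 0.1 × 20%) = 22% / 11% = 2.0.

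The ratio does not move. What is lost is events and precision.

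**4. Unequal monitoring.** Planned doses are 52 against 78, and months are 4 against 6; both ratios are 1.5. The documents give no reaction rates, so the risks here are assumed. With the same constant monthly rate in both arms, the 6-month risk is p6 = 1 − (1 − p4)^1.5:
- p4 = 5%: p6 = 7.4%, risk ratio 0.68.
- p4 = 10%: p6 = 14.6%, risk ratio 0.68.
- p4 = 20%: p6 = 28.4%, risk ratio 0.70.

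Under the same assumption, a true monthly rate 1.5 times higher on the fluoroquinolone would give 14.6% in both arms and be hidden.

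If reactions come early, the effect shrinks. Let f be the share of the 6-month cumulative hazard that falls in months 5–6. Then p4 = 1 − (1 − p6)^(1−f). With p6 = 10%:
- f = 0: ratio 1.00.
- f = 0.10: 9.05% / 10% = 0.91.
- f = 0.20: 8.08% / 10% = 0.81.
- f = 1/3 (constant rate): 6.78% / 10% = 0.68.

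**The case against.** **The rule was probably written with efficacy in mind, and an analysis plan may define a safety set.** No analysis plan is shown, so a missing definition alone would not be a fault. But this is a stated rule. As worded it covers every outcome, and a later plan would have to contradict it.

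**A reader might infer that dropping these patients distorts the comparison between arms.** The documents do not support that. If the cultures are pre-treatment, as they appear to be, the exclusion is unrelated to the allocated regimen. The number lost is also unknown. This objection stands.

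**A reader might also infer that tolerability will be compared over 4 against 6 months and that the result is therefore wrong.** That goes too far, for four reasons, all of which stand:
- The protocol does not say how reactions will be counted. The unequal count is inferred from the monitoring schedule.
- Duration is part of each regimen. Whole-course tolerability is a legitimate question, and reactions avoided by stopping earlier are a real difference.
- Regimen 3 falls from four drugs to two after month 2, so a constant rate through month 6 is not something the documents establish. The bias could be nil.
- Scheduled blood counts and chemistry fall at months 2 and 4 in every regimen, with urea and creatinine added at months 1 and 3 by the October 2005 amendment. The unequal period concerns clinical reactions and ECG only.

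**A hard cut at month 4 has faults of its own.** Treatment Regimens lets missed doses be made up for as long as 15 days past the fourth monthly examination in Regimens 1 and 2, so reactions to those doses could be missed. Under the November 2006 amendment, the affected Regimen 1 patients stop moxifloxacin and receive two further months of treatment, so exposure and observation time vary within that arm. A common window should therefore supplement the whole-course comparison and not replace it.

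**Conclusion.** The main point holds on the text. The culture rule, as worded, removes dosed patients from the adverse-reaction outcome, against the stated aim of assessing tolerability in smear-positive patients. The cost is lost safety information: 24–180 of 1200 patients and intervals 1–8% wider, if 2–15% are excluded (assumed). A systematic shift between arms is not shown, on the reading that the cultures are pre-treatment.

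The secondary point is conditional. If reactions are reported as crude whole-course percentages, regimens with equal monthly rates could show a risk ratio anywhere from 1.00 (no reactions in months 5–6) to about 0.68 (constant rate), in favour of the shorter regimens. Both ends are assumptions.

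**What to change.** **Patients section.** Confine the two-culture rule to efficacy and add a safety set, for example: *The requirement for two positive pre-treatment cultures applies to the efficacy analysis. Every patient who receives at least one dose of study treatment is included in the analysis of adverse reactions.* If pre-treatment cultures are not what was meant, the section should say which cultures apply.

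**Outcome measures, item (f).** State that adverse reactions are reported over the whole treatment course and, alongside, in a form that allows for duration: either a window common to all regimens or a rate per person-month on treatment. State how reactions to doses made up after month 4 are attributed, and how Regimen 1 patients changed by the November 2006 amendment are handled, for instance by showing time on and off moxifloxacin separately.

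**Cost.** A few sentences and one extra table. The change needs no new visits, tests or patients and leaves treatment unaltered.

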**Ethical Considerations:**

Patients will be informed in their mother tongue or a language that they understand, about the purpose of the study and the investigations that will be carried out to make a diagnosis and to monitor the response to treatment, and the frequency with which they will have to attend the treatment centre for supervised treatment. They will be informed of the drugs that will be used to treat them and the side effects that may occur due to the drugs. A Patient Information Sheet will be made available to the patient. Their consent will be obtained with reference to the investigations that will be carried out, the frequency of their attendance at the treatment centre, and their willingness to permit visits to their homes. Counseling will be done and a separate consent obtained before drawing blood for HIV antibody testing.

Any patient who does not respond to the treatment regimen and those who relapse during the period of follow-up will be treated with an appropriate regimen.

All diagnostic procedures and treatment will be entirely free for the patients.

Patients will be informed of their right to withdraw from the study at any time, without any penalty, if they so desired.

*Age of participants*:

There have been reports of the effect of fluoroquinolones on cartilage in animal experiments. Keeping this in view we had recruited only adult patients for the TRC ofloxacin studies. In this study also we will confine the study subjects to adults of 18 years and above, till there is categorical proof that moxifloxacin and gatifloxacin are safe for children, and do not affect bone growth.

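### Pregnancy is an exclusion, but no pregnancy test is listed at baseline, so an early unrecognised pregnancy can pass screening

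*Supplement*

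**What the plan says.** The Patients section sets the entry population broadly: "Patients aged 18 years and above residing in or around Chennai or Madurai will be eligible for enrollment to the study". It sets no restriction by sex and no upper age limit. The list of exclusions in the same section ends with "Pregnant or lactating women".

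The Baseline part of Clinical assessments and Investigations sets out how patients are screened. It opens with "History of present complaints and past medical history" and "Detailed clinical examination including testing for aquity of vision and colour vision", and goes on to sputum, chest X-ray, urine, ECG, blood counts, chemistry and HIV testing. The urine line reads "Urinalysis for albumin, sugar, bile pigments, acetyl isoniazid, rifampicin and for cytology". The chemistry line begins "Random blood sugar, blood urea, serum creatinine, serum uric acid, serum bilirubin" and continues with liver enzymes. The HIV line is "ELISA for HIV antibodies".

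None of these lines contains a pregnancy test, and a menstrual or pregnancy history is not named. The schedules for treatment and follow-up contain no pregnancy test either.

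**The concern.** An exclusion protects participants only as far as screening can detect the condition. A woman who knows she is pregnant can say so, and an established pregnancy may be found on examination. An early pregnancy that the woman herself has not recognised will often show up in neither. For such women the criterion has no means of being applied.

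What is at stake is, first, that the plan's own eligibility rule can be broken without anyone noticing and, second, the safety of the women concerned. The Background says that longer dosing of moxifloxacin and gatifloxacin still needs safety evaluation, since experience was limited to short courses. The trial regimens run for 4 or 6 months. Several collaborating clinics are named under Setting, so if the check is left to local habit it may differ between them.

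**Working it through.** The point needs no calculation, and the plan states no figure to reproduce. The check compares each exclusion, as amended, with the baseline items.

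| Exclusion | Baseline item that could detect it |
|---|---|
| HIV seropositive | ELISA |
| Abnormal ECG | 12-lead ECG read by a cardiologist |
| Hepatic or renal disease | Bilirubin and liver enzymes; urea and creatinine; clinical examination |
| Diabetes mellitus | Random blood sugar; urine sugar |
| Defective vision (added October 2005) | Acuity and colour vision testing |
| Anti-arrhythmic medication | Named in the baseline history |
| Seizures, psychiatric illness, moribund state | History and examination |
| Body weight below 30 kg | No weighing named at baseline |
| Lactation | History only, but known to the patient |
| Pregnancy | History and general examination only; no test named |

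Three further steps:

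1. **Later schedules.** During treatment, urine is tested for albumin and cytology. During follow-up it is tested for albumin, acetyl isoniazid, rifampicin and cytology. Neither schedule includes a pregnancy test.
2. **Amendments.** The 2005 amendment changes both the exclusions (defective vision) and the investigations (susceptibility testing; added urea and creatinine at months 1 and 3). The 2006 amendment changes regimen 1. Neither mentions pregnancy.
3. **Size.** The documents give neither the share of women of child-bearing age nor any pregnancy rate, so no count follows from them. Purely as an illustration, with both inputs assumed: if 20% to 35% of 1200 patients were women of child-bearing age and 1% to 3% of these had an unrecognised pregnancy, the range would be 1200 × 0.20 × 0.01 = 2.4 to 1200 × 0.35 × 0.03 = 12.6 women, or 0.2% to about 1% of the trial. The point does not rest on this range.

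**The case against.** The best counter-argument is that the baseline list is plainly not complete. Body weight below 30 kg is an exclusion, and weight also decides the rifampicin dose, yet the Baseline part names no weighing; weight appears only in the treatment and follow-up schedules. Weight must be known at entry all the same, so an item's absence from the list does not prove that the check is not made. Sites may likewise have tested for pregnancy without being told to. This stands to the extent that unwritten practice cannot be ruled out. It also means that pregnancy cannot be called the only testable exclusion without a named test. It does not close the gap. The need to know weight follows from other parts of the plan, whereas nothing in the plan implies a pregnancy test, and the urine and blood tests are listed individually.

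A reader might also draw stronger conclusions that the documents do not support:

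- **That pregnant women were enrolled.** The text shows only that this can happen. History and a detailed examination can still find an established pregnancy.
- **That the exclusion exists because of cartilage and bone effects.** The remark under Ethical Considerations, "There have been reports of the effect of fluoroquinolones on cartilage in animal experiments", justifies the lower age limit. It does not mention pregnancy, and the plan gives no reason for that exclusion.
- **That a pregnancy found later removes the patient from the allocated regimen or the evaluable number.** No rule says so; the plan is silent on pregnancy during treatment.
- **That two thirds of any such women would receive a fluoroquinolone.** The 2006 amendment ends moxifloxacin from 15.11.06, so from that date only one of the three regimens contains one.

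**Conclusion.** The gap is real but narrow. The plan excludes pregnant women and gives screening no test that would find an early unrecognised pregnancy, so such a woman can be enrolled and treated contrary to the criterion. The plan does name tests for most of the comparable exclusions, which makes this an internal mismatch between the eligibility list and the schedule.

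The number affected cannot be derived from the documents. The matter concerns eligibility and participant safety; it leaves the sample size and the efficacy comparison untouched. It is best treated as a cheap improvement.

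The conclusion assumes that the schedule is followed as written and that nothing on this point stands in the parts of the supplement that were not available for this review. A site manual or routine clinic practice that already included a test would reduce the practical risk, but the protocol would still need to say so.

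**What to change.** In Clinical assessments and Investigations, under Baseline, add a urine pregnancy test for women of child-bearing potential, done on the urine already collected, with the result available before allocation. The timing should be stated, because the schedule does not say when urine results are to be known relative to randomisation. Mention the test in the patient information described under Ethical Considerations, which covers the investigations to be carried out.

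The cost is the test strips, a short addition to the information sheet and a few more exclusions at screening. No extra visit or invasive procedure is needed. The test does not address conception during the 4 to 6 months of treatment, on which the plan is also silent.
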